##### **4.2. Exclusion criteria**

Those who meet any of the following items:

- Intracranial hemorrhagic diseases seen in head imaging: hemorrhagic stroke, epidural hematoma, intracranial hematoma, intraventricular hemorrhage, subarachnoid hemorrhage, etc; If it is only oozing blood, the researcher can judge whether it is suitable for inclusion;
- Severe disturbance of consciousness: the item score of La consciousness level of NIHSS was more than 1;
- Transient ischemic attack (TIA);
- Systolic blood pressure was still higher than 220mmhg or diastolic blood pressure was higher than 120mmhg after blood pressure control;
- Patients with severe mental disorders and dementia;

- Severe active liver diseases have been diagnosed, such as acute hepatitis, chronic active hepatitis, cirrhosis, etc; Or ALT or AST  $> 2.0 \times \text{ULN}$ ;
- Severe active kidney disease and renal insufficiency have been diagnosed; Or serum creatinine  $> 1.5 \times \text{ULN}$ ;
- After the onset of the disease, the drugs with neuroprotective effect in the manual have been used;
- Embolectomy or interventional therapy has been used or planned after the onset of the disease;
- Complicated with malignant tumor or undergoing anti-tumor treatment; For the subjects diagnosed with malignant tumor after enrollment, whether to continue to participate in the study can be judged by the researcher and the willingness of the subjects;
- Suffering from severe systemic diseases, the estimated survival time is less than 90 days;
- Allergic to d-borneol or edaravone or excipients;
- Patients during pregnancy, lactation, and planned pregnancy;
- Major operation history within 4 weeks before enrollment;
- Have participated in other clinical studies or are participating in other clinical studies within 30 days before randomization;
- The researcher thinks that it is not suitable to participate in this clinical study.

If a subject is found to have violated the inclusion criteria or met the exclusion criteria after enrollment, investigators may judge whether the subject is suitable to continue the study based on the risks and benefits.

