## **8.5. Safety analysis**

Data for safety evaluation include adverse events observed during the study and changes in laboratory data before and after treatment. Adverse event data are processed in statistical analysis after encoding according to the current version of MedDRA at the time of encoding.

Adverse events, adverse events during the study period since the first dose of the drug, major adverse events, unexpected adverse events, adverse event of special interest, serious adverse events, adverse events related to study drugs and serious adverse events related to study drugs are classified by system organ class and preferred term. Among them, significant adverse events are defined as adverse events that require drug therapy or non-drug therapy for the subject reporting the event; adverse events of special interest are divided into three types, i.e., liver function impairment, renal function impairment and hypokalemia. The Sponsor's clinical research associate is responsible for confirming and classifying all adverse events before unblinding.

If multiple adverse events occur in the same subject, the incidence rate is counted as 1 case; When the same AE occurs multiple times, the incidence of this AE is counted as 1. Adverse events will be summarized in frequency tables according to the system organ class (SOC) and preferred term (PT). The incidence is calculated by system, symptom/sign (count of cases: number of subjects who have experienced at least one adverse event).

The list of subjects experiencing adverse events and the list of subjects experiencing SAEs are provided. With respect to the laboratory data, in addition to the mean comparison before and after treatment, details of cases that are normal before treatment and abnormal after treatment or cases with abnormalities before treatment and abnormality exacerbation after treatment are mainly analyzed and listed. Refer to the statistical analysis plan for other details.

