## **2.7 Modification to the statistical analysis in the protocol**

Not available.

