**5) Data derivation and transformation:**

- Age: Year is used as unit, = (date of informed consent – date of birth)/365.25, rounded.
- Time from treatment to onset = time of first dose – time of stroke onset in hours (h) rounded to one decimal place.
- Stroke onset time is defined as the time at which the patient 's symptoms begin, and if it starts during sleep, the time at which the last manifestation is normal should be used as the time of onset. If stroke onset time is completely missing, impute with 0h0m on day of onset; if only minutes are missing, impute with 0m.
- Estimated glomerular filtration rate (eGFR):
- $eGFR (ml/min/1.73m^2) = 186 * (Scr/88.4)^{-1.154} * (age)^{-0.203} * 0.742$  (if female) \* 1.233

Where Scr is serum creatinine (umol/L), age is age, and female is female.

Renal function: normal renal function (baseline eGFR  $\geq$  90), mild renal impairment ( $60 \leq$  baseline eGFR < 90), and moderate to severe renal impairment (baseline e GFR < 60).

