### 4.4.2 Adverse Events

Adverse event data will be coded according to the current version of MedDRA. Treatment Emergent Adverse Event (TEAE) will be used in the analysis, while adverse events that start prior to the first dose of study medication (pre-treatment) will not be involved into the safety

analysis. Adverse events on study medication (during treatment) and after the last dose of study medication (post-treatment) will be analyzed.

The differences in the proportions of patients with AE between treatment groups and their corresponding 95% CIs will be estimated based on Newcombe–Wilson. The ORs and 95% CIs will be estimated with the logistic regression. Chi-squared test or Fisher’s Exact test will be used to compare the number of each AE combination according to system organ class and preferred term between treatment groups.

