#### **4.4.4 Vital Signs and Laboratory Test Examination**

Within each treatment group, the number and percentage of subjects with elevated in vital signs from baseline to day 14 after randomization will be described and Fisher’s Exact test will be used to compare the difference between treatment groups. The baseline measurements and changes after treatment of blood routine and bloodbiochemistry will be described as "abnormal and clinically significant" will be determined by the researchers. Within each treatment group, the number and percentage of subjects with an "abnormal and clinically significant" value will be summarized and Fisher’s Exact test will be used to compare the difference between treatment groups.

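### The laboratory Fisher test in SAP 4.4.4 does not exclude subjects already flagged at baseline, so a persisting baseline abnormality counts as an event and dilutes the comparison between arms

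*Combined protocol and SAP*

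**What the plan says.** SAP 4.4.4 has two parts. For vital signs it counts subjects "elevated in vital signs from baseline to day 14 after randomization", which gives both a reference point and a window. For blood routine and biochemistry the text begins "The baseline measurements and changes after treatment of blood routine and bloodbiochemistry will be described as" and then runs into a second clause that leaves the judgement of clinical significance to the researchers. It goes on to summarise the number and percentage of subjects with such a value and to compare arms by Fisher's exact test. The laboratory part names no visit and makes no reference to baseline status.

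Protocol 8.5 says that, besides a comparison of means, the laboratory work mainly analyses and lists "cases that are normal before treatment and abnormal after treatment or cases with abnormalities before treatment and abnormality exacerbation after treatment". It refers to the SAP for other details. SAP 2.7, headed "Modification to the statistical analysis in the protocol", declares no change.

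For adverse events the SAP does set a pre-dose rule. Under 4.4.2, "adverse events that start prior to the first dose of study medication (pre-treatment) will not be involved into the safety" analysis. SAP 4.1.3 defines baseline as the last non-missing value before the first dose, but the laboratory test does not use that definition.

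**The concern.** A test for harm should count what happened after treatment started. If a subject enters with a value the investigator already flags, and it is still flagged on Day 7, the wording of 4.4.4 lets that subject count as an event. Randomization spreads such subjects evenly on average, so there is no bias towards either arm. The cost is dilution: the same number of uninformative events is added to both arms, the odds ratio moves towards 1, and a real excess is more likely to return a non-significant p-value.

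This is the safety area where the protocol expects trouble. Section 1.3 describes liver and renal findings with edaravone, and 8.5 states that "adverse events of special interest are divided into three types, i.e., liver function impairment, renal function impairment and hypokalemia". Baseline abnormality is possible by design. Exclusion criterion 4.2 removes ALT or AST above 2.0 x ULN and serum creatinine above 1.5 x ULN, so milder elevations are eligible, and no numeric limit is set for other items such as glucose, potassium, CK or blood counts.

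**Working it through.** **Text.** Three rules compared:

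| Place | Baseline condition | Window |
|---|---|---|
| SAP 4.4.4, vital signs | Rise from baseline | To Day 14 |
| SAP 4.4.2, adverse events | Pre-dose onset excluded | During and after treatment |
| SAP 4.4.4, laboratory test | None stated | None stated |

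On the reading least favourable to the plan, pre-dose values themselves can count. On the sensible reading, only post-dose values count. A persisting baseline flag is an event under both.

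**Inputs.** From protocol 8.1: 457 per arm. This figure reproduces: 50% versus 40%, two-sided 0.05, 80% power and pooled variance give 388 per arm, and 388/0.85 = 456.5, hence 457. From SAP 4.4.4: Fisher's exact test, taken here at two-sided 0.05. *Assumed*, because the documents give no rates: new-flag rates of 7% (test) and 3% (control) among subjects not flagged at baseline; a fraction b flagged at baseline in each arm, all persisting.

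**Formula.** Event rate when baseline flags count = b + (1 − b) × new-flag rate. For b = 10%: test 0.10 + 0.90 × 0.07 = 16.3%; control 0.10 + 0.90 × 0.03 = 12.7%. Power is obtained by exact binomial enumeration.

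| b | Test | Control | Odds ratio | Power |
|---|---|---|---|---|
| 0 | 7.0% | 3.0% | 2.43 | 76% |
| 1% | 7.9% | 4.0% | 2.08 | 68% |
| 2% | 8.9% | 4.9% | 1.87 | 60% |
| 5% | 11.7% | 7.9% | 1.55 | 45% |
| 10% | 16.3% | 12.7% | 1.34 | 31% |
| 20% | 25.6% | 22.4% | 1.19 | 18% |

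Counting new flags only, among subjects not flagged at baseline, simulation (6,000 trials per setting) gives 76%, 74% and 67% at b = 5%, 10% and 20%. The loss in the table therefore comes almost entirely from the extra events. If only half of the baseline flags persist, power with them counted is 42% at b = 10% and 25% at b = 20%. With new-flag rates of 10% versus 5%, power is 79% at b = 0 and 41% at b = 10%.

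**One data set.** Suppose 46 subjects per arm (10%) are flagged at baseline and remain so, leaving 457 − 46 = 411. New flags of 29/411 versus 12/411 (7.1% versus 2.9%) give Fisher p = 0.010. Adding the 46 to each arm gives 75/457 versus 58/457 (16.4% versus 12.7%), p = 0.13. The excess is 17 subjects either way (29 − 12 = 75 − 58).

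**The case against.** The strongest defence is that clinically significant laboratory change is already compared elsewhere. Protocol 7.2.2 requires the investigator to record clinically relevant laboratory changes in the adverse event section of the CRF, and 7.3.1 classes clinically significant results that have deteriorated from baseline as adverse events. SAP 4.4.2 then compares treatment-emergent events between arms by organ class and preferred term. This stands, and it is the main reason the point is minor. A reader might infer that 4.4.4 is the only look between arms at laboratory harm; that is true only of the raw flag.

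Two other stronger readings are tempting. One is that the SAP deliberately counts pre-dose values as events. The sentence is broken, names baseline measurements and changes after treatment separately, and never says they are pooled. What can be said is that it does not exclude them. The other is that 4.4.4 contradicts protocol 8.5 without declaring it. But 8.5 describes listings, specifies no test between arms and defers to the SAP for detail, so the SAP adds a summary and cancels nothing. The difference lies in which cases each one picks out.

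The evidence on prevalence is also indirect. An eligible creatinine below 1.5 x ULN, or membership of the SAP's eGFR class below 60, is not the same as a value judged clinically significant. For a single parameter, 1% or 2% at baseline may be nearer the truth than 10% or 20%. Finally, 4.4.4 reports counts and percentages and attaches no decision rule to the p-value, so the excess itself stays visible.

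None of this supplies the missing baseline condition in the 4.4.4 test.

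**Conclusion.** The point holds as a gap in one event definition. As written, the laboratory test in SAP 4.4.4 does not exclude subjects flagged at baseline, and persisting baseline flags dilute the comparison even on a post-dose-only reading. Under the assumed 7% versus 3%, the power loss runs from 8 percentage points (76% to 68%) at 1% baseline flags to 58 points (76% to 18%) at 20%. The size depends entirely on flag and persistence rates that the documents do not give. The consequence is a less sensitive supplementary safety test. The efficacy analysis is untouched, and the adverse event comparison offers a parallel route to the same signal. This is a cheap improvement to consider, with medium confidence in how much it would matter.

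**What to change.** In SAP 4.4.4, define the laboratory event per parameter:

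- **Numerator:** safety-set subjects with a value flagged abnormal and clinically significant at a scheduled post-dose visit (Days 7, 14, 30, 90) who either were not flagged at baseline or whose baseline abnormality worsened by CTCAE v5.0 grade, the scale already adopted in protocol 7.3.5.
- **Denominator:** safety-set subjects with a baseline value and at least one post-dose value of that parameter.
- **Unscheduled values:** state whether they count.

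The IDMC minutes of December 2022 record agreement to lock the database. If unblinding has occurred, report this count beside the one 4.4.4 now specifies and label both.

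The cost is one more definition and one more table. No new sample or visit is needed, since 7.2.2 already has the investigator evaluate each laboratory report. This assumes the baseline flag was captured; if it was not, the reference range at baseline can stand in. The worsening rule has to stay, because counting new flags alone would miss deterioration in subjects already abnormal.

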### 1.3. Risk

Based on the available evidence, this product has potential clinical efficacy in improving prognostic neurological function in patients with acute ischemic stroke. It was confirmed in the phase III trial (SIM-23-02 trial) that the clinical efficacy of concentrated solution of edaravone dexborneol for injection, which has similar active ingredients of this product, was significantly superior to that of edaravone injection. The results of the SIM-23-02 trial showed that the proportion of participants with mRS score  $\leq 1$  on Day 90 in the group of concentrated solution of edaravone dexborneol for injection (65.61%) was much higher than that in the group of edaravone injection (57.48%). The difference between the two groups was 8.13%, and the 95% CI was (2.63% ~ 13.63%, P = 0.0039). The mean differences from baseline in NIHSS scores were -2.97, -3.99, and -4.81 respectively on days 14, 30, and 90 after treatment in the edaravone dexborneol group, and -2.56, -3.60, and -4.49 respectively in the edaravone group. The differences from baseline were statistically significant in both

groups. The mean differences of decrease in NIHSS scores between the edaravone dexborneol group and the edaravone group on days 14, 30, and 90 were -0.41 (95%CI: -0.73~ -0.09,  $P = 0.0097$ ), -0.39 (95%CI: -0.71~ -0.07,  $P = 0.0151$ ), and -0.32 (95%CI: -0.64 ~ -0.01,  $P = 0.0370$ ), respectively. The differences between the two groups were statistically significant.

When edaravone was approved for marketing in Japan, clinical trials showed that there were 26 cases (4.57%) of adverse reactions in 569 cases in total, and the main adverse reactions were liver dysfunction in 16 cases (2.81%), allergy in 6 cases (1.05%), and rash in 4 cases (0.70%). Among the 569 cases, 122 (21.4%) were considered to have laboratory abnormalities, mainly including increased AST (GOT) (43/558 cases: 7.71%), increased ALT (GPT) (46/559 cases: 8.23%), and other abnormal liver function test.

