#### **Severity of adverse events and serious adverse events**

The severity of all AEs is evaluated using the NCI Common Terminology Criteria for Adverse Events (CTCAE) Version 5.0 in this study. For AEs not defined in the NCI-CTCAE, the following rules will be referred to determine the severity:

|         |                                                                                                            |
|---------|------------------------------------------------------------------------------------------------------------|
| Grade 1 | Mild; asymptomatic or mild symptoms; clinical or diagnostic observations only; intervention not indicated. |
|---------|------------------------------------------------------------------------------------------------------------|

|         |                                                                                                                                                                                                                                                                                               |
|---------|-----------------------------------------------------------------------------------------------------------------------------------------------------------------------------------------------------------------------------------------------------------------------------------------------|
| Grade 2 | Moderate; minimal, local or noninvasive intervention indicated; limiting age-appropriate instrumental activities of daily living, such as preparing meals, shopping for groceries or clothes, using the telephone, managing money, etc.                                                       |
| Grade 3 | Severe or medically significant but not immediately life-threatening; hospitalization or prolongation of hospitalization indicated; disabling; limiting self care ADL (referring to bathing, dressing and undressing, feeding self, using the toilet, taking medications, and not bedridden). |
| Grade 4 | Life-threatening consequences; urgent medical intervention indicated.                                                                                                                                                                                                                         |

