## **4 Statistical Analysis**

### **4.1 General Principles**

All statistical analyses for this study will be performed using the statistical analysis software SAS version 9.4 or higher. All data collected in Case Report Form (CRF) will be statistically calculated by treatment groups. For continuous variables, the number of subjects with non-missing data, mean, standard deviation, median, minimum, and maximum were calculated and listed. The number of decimal places for the minimum and maximum values will be

consistent with that recorded in the database. Means, medians, and standard deviations will be rounded to one more decimal place than the raw data recorded in the database. For discrete variables, frequencies and percentages were calculated and presented. Percentages will be presented to one decimal place.

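### The only formal between-arm test of laboratory values rests on an undefined investigator label, and the SAP does not carry through the protocol's shift analysis or its three events of special interest

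*Combined protocol and SAP*

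**What the plan says.** Changes in laboratory data are a named safety endpoint (protocol 2.2.3, SAP 2.3).

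- **SAP 4.4.4.** One sentence reads "The baseline measurements and changes after treatment of blood routine and bloodbiochemistry will be described" and then runs, without a break, into a statement that the researchers decide what is abnormal and clinically significant. The section continues with "the number and percentage of subjects with an 'abnormal and clinically significant' value will be summarized", compared between arms by Fisher's exact test. It names no analyte, multiple of the upper limit of normal (ULN) or grade.
- **SAP 4.1.** "All data collected in Case Report Form (CRF) will be statistically calculated by treatment groups", with mean, SD, median, minimum and maximum for continuous variables.
- **SAP 4.4.2.** Adverse events are compared between arms by system organ class and preferred term.
- **Protocol 8.5.** Besides a before/after comparison of means, the main laboratory work is on "details of cases that are normal before treatment and abnormal after treatment", together with pre-existing abnormalities that worsen. Liver impairment, renal impairment and hypokalemia are the events of special interest. Other details are left to the SAP.
- **SAP 2.7.** Under modifications to the protocol's analysis: "Not available".
- **Protocol 6 and Table 7.2-1.** ALT, AST, bilirubin, creatinine and potassium are measured at screening and on days 7, 14, 30 and 90.
- **Protocol 7.3.5.** Severity of adverse events is graded by the "NCI Common Terminology Criteria for Adverse Events (CTCAE) Version 5.0".

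**The concern.** Protocol 1.3 presents liver and renal effects as the known risks of edaravone, so a reader will look for a between-arm comparison of enzymes and creatinine. The plan's one formal test of laboratory values counts a patient only if a local investigator applied a label that no document defines. Laboratory data come from the sites (protocol 7.2.2), of which about 40 were planned, so the label may mean different things in different places.

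The adverse-event tables do not give an independent route. Under protocol 7.3.1 a laboratory abnormality becomes an adverse event only if the investigator judges it clinically significant, and abnormalities put down to underlying disease are normally excluded. Both tested routes therefore pass through the same judgement.

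The analysis that would not depend on that judgement, the shift analysis of protocol 8.5, has no counterpart in SAP 4.4, and the special-interest categories do not appear there. At stake is how far a finding of no laboratory difference can be trusted.

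**Working it through.** **Step 1. Which by-arm laboratory outputs are planned, and which are tested.**

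| Output | Source | By arm | Between-arm test |
|---|---|---|---|
| Values and changes described | SAP 4.4.4, 4.1 | yes | none stated |
| Patients with the investigator's label | SAP 4.4.4 | yes | Fisher |
| Adverse events by class and term | SAP 4.4.2 | yes | chi-squared or Fisher; entry by investigator judgement |
| Normal-to-abnormal and worsening cases | protocol 8.5 only | not stated | none stated |
| Three special-interest categories | protocol 8.5 only | not stated | none stated |

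Means can hide a minority of patients with marked rises, and a maximum gives no count. The descriptive rows are therefore no substitute for a threshold or shift comparison.

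**Step 2. Arm size.** The plan's figure is 388 per group for 50% against 40%, two-sided 0.05, 80% power. The pooled two-proportion formula without continuity correction gives 388. Allowing for 15% dropout, 388 / 0.85 = 456.5, rounded up to 457. Both figures reproduce.

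**Step 3. Anchor rates (protocol 1.3, earlier Japanese edaravone trials).** Raised ALT: 46/559 = 8.23%. Liver dysfunction recorded as an adverse reaction: 16/569 = 2.81%. Ratio: 2.81 / 8.23 = 0.34. The numerator also required attribution to the drug, which this trial's label does not, so 34% is a low-end assumption for the share of rises labelled. It is not an estimate.

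**Step 4. Illustration.** Let s be the share of rises that receive the label, assumed equal in both arms. The observed rates are then s × 8.23% and s × c, where c is the placebo rate. The documents give neither s nor c. Exact power of Fisher's two-sided test at 0.05, 457 per arm:

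| s | c = 4%: expected counts | power | c = 5%: expected counts | power |
|---|---|---|---|---|
| 1 (all rises count) | 37.6 v 18.3 | 73% | 37.6 v 22.9 | 45% |
| 0.50 | 18.8 v 9.1 | 40% | 18.8 v 11.4 | 22% |
| 0.34 | 12.8 v 6.2 | 26% | 12.8 v 7.8 | 15% |

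For example, 457 × 0.0823 = 37.6 and 457 × 0.04 = 18.3.

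**Step 5. How fragile this is.**
- *Higher placebo rate.* With every rise counted, power is 22% at c = 6% and 9% at c = 7%, so numeric counting would usually miss the difference too.
- *Unequal capture.* Suppose the label catches 34.2% of background rises but 70% of the drug-caused excess, as it might if larger rises are labelled more often. At c = 4% the placebo rate becomes 0.342 × 4% = 1.4%. The active rate becomes 1.4% + 0.70 × (8.23% − 4%) = 4.3%. Power is 74%, against 73% on all rises: the loss disappears.

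**The case against.** The strongest case on the other side has five parts.

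1. *Laboratory data are not seen only through the label.* SAP 4.1 and 4.4.4 describe values and changes by arm, SAP 4.4.2 tests adverse events by preferred term, and protocol 8.5 plans mean comparisons and listings. This stands. The point is confined to the formal test of laboratory values, and to what SAP 4.4 leaves out.
2. *SAP 2.7 can be read as leaving protocol 8.5 in force.* Protocol 8.5 also promises no between-arm test of shifts, so no such test was dropped. This stands too. But 8.5 hands the detail to the SAP, and the SAP has no table for either item.
3. *The documents show neither under-counting nor bias.* A reader might infer that most rises go unlabelled, or that the safety comparison is distorted. No section gives a capture rate. The label is applied under double-blinding, with randomisation stratified by site, so differing site habits should balance between arms. Lost sensitivity is the most that can be claimed.
4. *The power figures do not measure this trial.* Placebo rates and capture are assumed. The meta-analysis of ten randomised trials described in protocol 1.3 found no significant difference in raised aminotransferases or abnormal renal function. Accepted: the figures illustrate a mechanism only.
5. *The data may not be ready for grading.* Nothing says that local reference limits are in the database, and CTCAE is adopted for adverse events, not for raw values. This stands, and the fix is conditional on it.

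The garbled sentence in SAP 4.4.4 may also have lost a phrase, which is a further reason to repair it before relying on any reading of it.

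**Conclusion.** The point holds as a gap between protocol and SAP and as a weakness of method. The sole formal test of laboratory values uses an undefined label, and neither the normal-to-abnormal and worsening analysis nor the three special-interest categories of protocol 8.5 is carried into SAP 4.4. Laboratory signals may therefore be missed.

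The effect to expect is lower sensitivity, and its size cannot be computed from the documents. The illustrated fall in power, from 73% to between 40% and 26% at a 4% placebo rate and from 45% to between 22% and 15% at 5%, rests on three assumptions: the placebo rate, the share labelled, and equal capture of background and drug-caused rises. Relaxing the third can remove the loss altogether.

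The stronger reading, that the plan will produce a wrong safety conclusion, is not supported. This is a change that should be made because it is cheap and serves a named safety endpoint.

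**What to change.** - Rewrite the garbled sentence in SAP 4.4.4 so that the description of values and the definition of the label are separate.
- Add by-arm tables of the shift from baseline to worst post-dose value for ALT, AST, bilirubin, creatinine and potassium. Use CTCAE v5.0 grades or ULN multiples, for those analytes where the sponsor confirms that local limits are available.
- Report the proportion in each arm with any treatment-emergent worsening and with grade 2 or higher, with risk differences and 95% confidence intervals.
- Add a by-arm table of the three special-interest categories of protocol 8.5.
- Keep the investigator's label as a supporting table.

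The cost is a few sentences and tables on measurements already scheduled at every visit, plus a check on how local limits are held. More low-grade abnormalities will be reported. The third IDMC minutes record agreement to lock the database, so anything added after unblinding must be labelled as such. It can be noted that the shift cases and special-interest categories were already in protocol 8.5.
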